**1. OVERVIEW**

We will develop, deliver and evaluate a solar powered tablet-based motivational interviewing HIV/Sexually Transmitted Infection (STI) intervention at internally displaced persons (IDP) camps in Leogane, Haiti. Women from IDP camps will be trained as community health workers to deliver the HIV/STI intervention to women in IDP camps working in collaboration with NEGES, a community development organization.

**2. BACKGROUND**

Haiti has the highest HIV infection rate in the Western Hemisphere, with 1 in 50 people infected (UNAIDS, 2011). Almost half (46%) of people living with HIV (PLHIV) in the Caribbean live in Haiti (UNAIDS 2011b). The January 2010 earthquake led to the collapse of Haiti’s social, economic and health infrastructure. One year following the earthquake, UNICEF (2011) reported

that one million people remain displaced, living in approximately 1,200 IDP camps. UNICEF’s January 2011 report noted that there is currently no organization responsible for community based HIV prevention, condom distribution or HIV/AIDS education in IDP camps in Haiti.

Women who live in IDP camps are at particularly high risk for HIV infection and sexually transmitted infections (STI) due to limited access to reproductive health services, the collapse of social infrastructure and community networks, increased poverty and sexual violence (IASC, 2010; MADRE, 2011; UNAIDS, 2011b).

It is integral to involve women’s grassroots organizations in the planning and delivery of HIV prevention interventions and strategies to reduce sexual violence to ensure their success (MADRE, 2011). There is an urgent need for more information on HIV risk and prevention in the context of violence among women in Haiti’s IDP camps (UN Women, 2011).

The deleterious impact of HIV and AIDS is exacerbated due to a weak health care system, extreme poverty and HIV-related stigma (UNAIDS, 2010). Haiti is the poorest country in the Western hemisphere: in 2009 it ranked 145th out of 169 countries on the United Nations Development Programme’s Human Development Index. Poverty and a lack of employment opportunities pose serious barriers to health and well-being. In Haiti less than half (43%) of

PLHIV have access to anti-retroviral treatment, and only 60% of HIV-positive women have access to anti-retrovirals (ARV) for preventing perinatal HIV transmission (UNAIDS, 2010).

Even before Haiti’s 2010 earthquake, women and girls were at higher risk for HIV infection. Young women aged 15-24 have HIV infection rates double those among young men (UNAIDS, 2010). Knowledge regarding HIV/AIDS is very low in Haiti: approximately one-third of young men and women aged 15-24 could correctly identify HIV prevention methods and reject major HIV transmission misconceptions (UNAIDS, 2010). Young women had lower knowledge rates

(34%) than young men (40%). More women (79%) than men (66%) aged 15-49 who had more than one sexual partner in the past 12 months did not report condom use during their last sexual encounter (UNAIDS, 2010). Only 8% of women and 5% of men aged 15-49 reported receiving an HIV test in the last 12 months and knowing their status (UNAIDS, 2010). Research with youth

(n=3391) in Port-au-Prince reported HIV infection was associated with: lower levels of education, STI infection, having a child, not living with one’s parents; this study also found that most youth had never used a condom (Dorjgochoo et al., 2009). Authors highlighted an acute need for HIV prevention services targeting youth, with a particular focus on building self-esteem and sexual negotiating skills among girls and young women (Dorjgochoo et al., 2009).

Developing a women-focused community-based model of HIV prevention in IDP camps in Haiti has implications for Canada’s HIV prevention work globally. There are over one million IDP in Haiti, and over 27 million IDP globally (IDMC, 2011): this study can therefore inform HIV prevention research/programming in Haiti and can be tested for applicability in other IDP camps globally. Researchers have highlighted the need for creative partnerships to share skills and HIV

care models between developed and developing countries (Ivers et al., 2010). Struggles to meet basic needs for survival and sexual violence have been highlighted as drivers of HIV among IDP in Uganda (Rujumba & Kwiringa, 2010), so lessons learned may inform global HIV prevention.

Global HIV work in IDP camps has focused on measuring HIV incidence, distributing condoms, or ARV distribution (Hampton, 2008; Khaw et al., 2000)—less research has focused on cultural, gender and context appropriate HIV prevention strategies for women (Spiegel, 2004).

**3. OBJECTIVES**

This study aims to:

1. Understand levels of: HIV/STI knowledge and risk factors; coping (social support, resilient coping); mental health issues (trauma, depression); and relationship power
2. Assess the influence of individual and group educational sessions on: HIV/STI knowledge and risk; coping (social support, resilient coping); mental health issues (trauma, depression); relationship power
3. Conduct a community forum with partners, health researchers and knowledge users in Leogane, Haiti to share HIV/AIDS information and study findings

**4. RESEARCH QUESTIONS**

1. What are the levels of: HIV/STI knowledge, HIV/STI risk factors, mental health issues, coping, and relationship power among women living in IDP camps in Leogane, Haiti?
2. Holding all other effects constant, is there a significant difference in outcomes (HIV/STI knowledge, HIV/STI risk factors, mental health issues, coping, relationship power) among women living in IDP camps before and after a peer health worker delivered HIV/STI intervention?

**5. METHODOLOGY**

**5.1 Overall approach**

We will develop and field test a solar-powered tablet technology that synchronizes HIV/STI prevention messages with a participant’s responses in Leogane, Haiti. The tablet will be programmed to analyze the data and to generate a brief video-based counseling message for the peer health worker (PHW) and participant that involves HIV/STI risk reduction strategies.

A pre and post-test N-of-1 trial design will be used. Outcomes (HIV/STI knowledge, HIV/STI risk factors, mental health issues, coping, relationship power) will be measured at baseline and 3 months post-intervention. Participants (n=200) will receive a high intensity HIV/STI educational intervention: a) tablet-based intervention using an HIV/AIDS educational video; b) 6 weekly sessions of women’s health discussions. The control group will include the same group by testing the outcomes at baseline.

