***(5) Conducting weekly women’s health meetings***

Each PHW (n=8) will conduct a 2-hour women’s health meeting at NEGES once a week for 6 weeks. Meetings will be held when NEGES is closed and each PHW will conduct meetings at different times: this will help to ensure privacy. Each PHW will carry out the 6 meetings with the 25 women they conducted the pre test with. Participants will receive an honorarium for each session attended and food and refreshments will be provided. PHW will have a training manual with the outline for each session, including: learning points, a case study, activities and discussion questions. Each session will begin with ground-rules and discussions about confidentiality (e.g. importance of not sharing individual’s comments from the discussion outside of the meeting).

Weekly meetings will address: (1) sexual health: HIV/AIDS; (2) sexual health: sexually transmitted infections; (3) interpersonal relationships; (4) communication and decision-making skills; (5) mental health and well-being; (6) coping skills. Limits of confidentiality will also be discussed with participants, in particular participants will learn that confidentiality cannot be guaranteed during group meetings and to keep this in mind when they are sharing personal information. Sessions will be conducted in Haitian Creole, and PHW will record notes following each session regarding any questions or points that need clarification. The coordinator will meet with the PHW weekly to provide support, clarification and any guidance requested.

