**5.5 Data Collection and Analysis**

The surveys will be administered in Haitian Creole, the primary language in Haiti. The survey will be developed in English, translated into Haitian Creole, back-translated into English, and finalized in Haitian Creole. The surveys will be programmed into a tablet; each PHW will be assigned one tablet for the duration of the study. Once the PHW have completed each survey, they will return the tablet to a locked filing cabinet at NEGES. The survey results will be entered into the password-protected tablet. Following the survey, the PHW will save the data from the tablet on a password protected, encrypted USB key in the locked filing cabinet in NEGES. Each PHW will be assigned their own: USB key (password protected, encrypted), tablet, and codesheet. Only the study coordinator will have access to the locked filing cabinet at NEGES.

The principal investigator will travel to Haiti during the pre (January 2012) and post-test (April 2012) data collection. After data collection is completed for the pre-test, the data will be removed by the principal investigator from the tablets and USB keys and stored on a password protected laptop password-protected computer, specifically into an SPSS database. After data collection is completed for the post-test, the data will be removed by the principal investigator from the tablets and USB keys and stored on a password protected laptop password-protected computer, specifically into an SPSS database.

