**5.8.2 MANOVA Analyses**

Multivariate analysis of variance (MANOVA) will be used to assess pre and post-test differences across outcome variables. Separate MANOVA analyses will be conducted for primary outcome variables focused on HIV/STI (HIV knowledge, STI knowledge, HIV/STI risk factors, relationship power) and secondary outcome variables focused on mental health (depression, trauma, resilient coping, social support). We will compare differences in participant scores from the pre-test and post-test (after the 6-weekly health meetings) to assess if the intervention influenced any of the primary or secondary outcomes. We will conduct a multivariate analysis of covariance (MANCOVA) to control for the number of weekly health meetings attended. Significant MANCOVA will be followed up with both univariate tests and discriminant function analyses (DFA) to understand significant effects. DFA can be used to identify variates (combinations of dependent variables) and how the dependent variables contribute to the variates. Analyses will be conducted using SPSS 19 software.

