**8. TIMELINE 2011-2012**

| **TASK** | **J** | **A** | **S** | **O** | **N** | **D** | **J** | **F** | **M** | **A** | **M** |
| --- | --- | --- | --- | --- | --- | --- | --- | --- | --- | --- | --- |
| Develop survey | **X** |  |  |  |  |  |  |  |  |  |  |
| Submit ethics | **X** |  |  |  |  |  |  |  |  |  |  |
| Develop training manual/videos |  | **X** | **X** | **X** |  |  |  |  |  |  |  |
| Train women as peer health workers |  |  |  |  | **X** |  |  |  |  |  |  |
| Study recruitment |  |  |  |  |  | **X** |  |  |  |  |  |
| Pre-test data collection |  |  |  |  |  |  | **X** |  |  |  |  |
| Weekly women’s health meetings |  |  |  |  |  |  |  | **X** | **X** |  |  |
| Post-test data collection |  |  |  |  |  |  |  |  | **X** | **X** |  |
| Community forum and knowledge translation |  |  |  |  |  |  |  |  |  |  | **X** |

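### Section 5.1 sets the post-test three months after the intervention, but the protocol's own calendar allows at most 54 days after the last meeting

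*Protocol*

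**What the plan says.** Four places in the protocol bear on when the post-test happens.

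- **Section 5.1** says that outcomes "will be measured at baseline and 3 months post-intervention". The same paragraph defines the intervention as a tablet-based video component plus "6 weekly sessions of women’s health discussions".
- **Section 5.3.1, activity (5)**, gives the pace: each peer health worker "will conduct a 2-hour women’s health meeting at NEGES once a week for 6 weeks".
- **Section 5.5** has the principal investigator in Haiti "during the pre (January 2012) and post-test (April 2012) data collection".
- **Section 5.8.2** compares scores from the "pre-test and post-test (after the 6-weekly health meetings"). It gives the order but no interval.
- **Section 8** is a month-level chart. The pre-test is marked in January, the meetings in February and March, the row "Post-test data collection" in March and April, and the community forum in May.

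Section 5.3.1, activity (3), hires the peer health workers, who administer the post-test, from November to May.

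**The concern.** Because section 5.1 makes the six sessions part of the intervention, time after the intervention has to run from the last session. On the dated calendar, the post-test comes within weeks of that session.

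HIV knowledge is the primary outcome, and the first weekly meeting teaches it directly. A score taken a few weeks after the programme and a score taken three months after it answer different questions. A report that repeats section 5.1 would give readers the wrong follow-up time for the main result.

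This is more than a visit window left for an analysis plan to define. The protocol states an interval that its own schedule cannot produce. Sections 5.5 and 8 also differ from each other on the post-test window: April alone against March and April.

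**Working it through.** **Inputs**

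- Stated interval: 3 months after the intervention (section 5.1).
- Six weekly meetings (sections 5.1 and 5.3.1): first to sixth is 5 × 7 = 35 days.
- Meetings in February and March, post-test in March and April, forum in May 2012 (section 8).
- Pre-test in January 2012, post-test in April 2012 (section 5.5).
- Assumption: a mark in a month means any day of that month. February 2012 has 29 days.

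**1. Date of the sixth meeting.** Earliest: 1 February + 35 days = 7 March 2012. Latest: 31 March 2012, the last day of the marked months.

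**2. Gap from sixth meeting to post-test.**

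- April post-test (section 5.5): minimum 1 April − 31 March = 1 day. Maximum 30 April − 7 March = 24 + 30 = 54 days, and 54 / 7 = 7.7 weeks.
- March–April post-test (section 8): the maximum is again 54 days. The month marks alone would allow 1 March − 31 March = −30 days, but the order in section 5.8.2 rules out a negative gap, so the minimum is about 0.
- If the programme is counted as six full weeks (42 days), it ends no earlier than 14 March. The maximum is then 17 + 30 = 47 days, or 6.7 weeks.

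The stated 3 months is not reproduced under any of these readings.

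**3. Where three months would fall.** 7 March + 3 months = 7 June; 31 March + 3 months = 30 June. The earlier date is 38 days after 30 April, the last scheduled post-test day. It is also after the May forum and after the peer health workers' hire ends.

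**4. Working backwards.** For a test on 30 April to be three months after the last meeting, that meeting would have to be held by about 30 January. The first would then be by 30 January − 35 days = 26 December 2011, before the January pre-test.

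**5. What three months does fit.** Pre-test to post-test, mid-month to mid-month: 15 January to 15 April = 16 + 29 + 31 + 15 = 91 days. The full ranges are:

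| Post-test window | Shortest | Longest |
|---|---|---|
| April only | 31 January to 1 April: 29 + 31 + 1 = 61 days | 1 January to 30 April: 30 + 29 + 31 + 30 = 120 days |
| March–April, after the sixth meeting | 31 January to 8 March: 29 + 8 = 37 days | 120 days |

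The shortest March–April case takes the day after the earliest possible sixth meeting. So three months after baseline describes an April post-test roughly, and a March post-test poorly.

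**The case against.** The best defence is that one phrase is out of line and nothing else depends on it. There is one pre-test and one post-test. Sections 5.5, 5.8.2 and 8 can be read together as after the meetings, in March or April 2012, and April alone in section 5.5 may reflect only when the principal investigator travels. The before-after comparison, the sample size and the MANOVA do not use the three-month figure. It is even correct for the video shown after the January survey. Most of this stands and limits the severity. It does not rescue the phrase, because section 5.1 counts the six sessions as part of the intervention.

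A reader might infer more than the documents support:

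- **That women will be tested before their sixth session**, because meetings and post-test share March. The chart is only month-level, each peer health worker runs a separate group, and section 5.8.2 puts the post-test after the six meetings. The shared month may be overlap between groups.
- **That the trial makes a false claim of retained knowledge.** The objectives and research questions ask about the influence of the sessions and a before-after difference. None mentions durability. The error arises only if results are reported in section 5.1's words.
- **That the knowledge gain will be overstated by some factor.** The protocol gives nothing on how fast knowledge fades, so no factor can be derived.
- **That June lies outside the study.** The coordinator is hired for a study duration of 18 months, longer than the chart. June is outside the scheduled post-test, the forum date and the peer health workers' hire, but not shown to be outside the study.

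**Conclusion.** The contradiction holds. The protocol states a follow-up of three months after the intervention, and its calendar gives about 0 to 54 days (at most 7.7 weeks) after the last meeting. The result needs only two assumptions: that a month mark means any day in that month, and that the intervention ends with the sixth session, as section 5.1's definition implies. The likely source is the January-to-April interval between the two surveys.

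The consequence is a misstated follow-up time for the primary outcome if section 5.1 is carried into a report. The analysis itself is not invalidated. This should be fixed, but it does not threaten the trial.

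**What to change.** Reconcile sections 5.1, 5.5, 5.8.2 and 8 to one anchor event and one window.

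- **If the calendar stands:** in section 5.1, replace the three-month phrase with wording such as: after the group's sixth meeting and within about 8 weeks of it. State the baseline-to-post-test interval as whatever the chosen window gives: 61 to 120 days for April only, about 37 to 120 days for March–April.
- **Window:** make sections 5.5 and 8 agree on April or on March–April.
- **Order:** if March is kept, apply section 5.8.2's order to each group, so that no group is post-tested before its sixth meeting.
- **Dates:** record the date of each post-test and of each group's sixth meeting, so that the actual interval can be reported. Do this at the time, because the sheet linking ID numbers to participants is destroyed after the post-test.
- **If the outcome three months after the meetings is what is wanted:** the post-test and forum dates must move, and the peer health workers' hire would need to cover the later post-test.

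Keeping the calendar costs some wording, a date field and a small scheduling constraint in March. Moving the post-test would cost more, and is needed only if the longer follow-up is the intended question.

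### A single-group before-after study is labelled an N-of-1 trial with a control group, and its changes are attributed to the intervention

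*Protocol*

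**What the plan says.** Section 5.1 of the protocol names the design: "A pre and post-test N-of-1 trial design will be used". It describes the comparator as follows: "The control group will include the same group by testing the outcomes at baseline". The same section says who is treated, "Participants (n=200) will receive a high intensity HIV/STI educational intervention", and when outcomes are taken: they "will be measured at baseline and 3 months post-intervention".

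Three other places state what the comparison is meant to show:

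- Objective 2 in section 3: "Assess the influence of individual and group educational sessions on", followed by the list of outcomes.
- Research Question 2 in section 4: "Holding all other effects constant, is there a significant difference in outcomes", comparing women before and after the intervention.
- Section 5.8.2: "Multivariate analysis of variance (MANOVA) will be used to assess pre and post-test differences across outcome variables". Scores are compared "to assess if the intervention influenced any of the primary or secondary outcomes". The one covariate named, in a MANCOVA, is the number of weekly meetings attended.

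Nothing in the protocol text at hand limits these statements to change over time or names a rival explanation for a change.

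**The concern.** An N-of-1 trial compares treatment and control periods within one person, usually repeated, and is read person by person. A control group shows what happens without the intervention over the same period. Section 5.1 claims both features, and the study it describes has neither.

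The labels matter because of the inference built on them. If a reader accepts that there is a control and that other effects are held constant, a difference between the two surveys becomes evidence that the programme worked. An uncontrolled before-after comparison can show that scores changed; it cannot show why. The findings go to a community forum meant to help set priorities for programmes (section 5.3.1, activity 6), and section 7.2 hopes they can serve as an evidence base for policy and practice. What the study may claim should therefore be settled in the protocol.

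**Working it through.** **1. Label against design.**

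| Feature | What the label implies | What the protocol provides |
|---|---|---|
| Periods per person | Treatment and control periods within the person | One pre-test, one programme, one post-test (5.1) |
| Level of analysis | The individual | Group-level MANOVA (5.8.2) |
| Control | Outcomes without the intervention over the same time | The same women's baseline scores (5.1) |
| Untreated women | Some, or untreated periods after baseline | None; all 200 are to receive the intervention (5.1) |

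The baseline score is one half of the change score. It says nothing about where these women would have been at post-test without the programme.

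**2. Is anything held constant?** The only adjustment named is for meetings attended. That is the amount of intervention received, and it is determined after baseline. Conditioning on it fixes no outside influence.

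**3. Rival explanations that follow from the protocol's own procedures.**

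- *Retest familiarity.* The same women answer the pre-test and post-test survey, linked by ID number.
- *Interviewer.* Each peer health worker gives the pre-test and post-test to 25 women and also leads their six meetings (5.3.1, activities 4 and 5). Answers on condom use, relationship power or mood may shift because of who is asking.
- *Calendar change.* Section 5.5 dates the two rounds January and April 2012. Anything else that changed between them falls wholly into the pre-post difference.

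**4. Illustration of size.** The protocol gives no alpha, power, effect size, SD or drift for this comparison, so there is no planned figure to reproduce. The one input taken from it is n=160, the minimum sample in section 5.6.1. (The rule stated there gives 7 × 20 = 140, not 160. That is a separate matter and nothing here depends on it.)

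Assumptions: a univariate paired test, two-sided alpha 0.05, women independent, true intervention effect zero, and a drift from other causes of d SDs of the change score. By the normal approximation:

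P(significant) = Φ(d√n − 1.96) + Φ(−d√n − 1.96)

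With √160 = 12.65 and d = 0.22: d√n = 2.78, 2.78 − 1.96 = 0.82, and Φ(0.82) ≈ 0.79. The second term is negligible, so the result is about 80%.

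| Drift d | n=160 | n=200 |
|---|---|---|
| 0 | 5% | 5% |
| 0.1 | 24% | 29% |
| 0.2 | 72% | 81% |
| 0.3 | 97% | 99% |

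With a concurrent control group sharing the same drift, the rate would stay at 5% in every row. The table shows what is lost without one. It does not show that drift of any given size will occur.

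**The case against.** The strongest reply is that nothing is hidden. Section 5.1 says openly that the control is the same women at baseline, so a careful reader sees that there is no separate group. The section also describes the work as a field test, for which a single-group pre-post design is legitimate. Research Question 2 asks about a difference before and after, and the word causal appears nowhere. All of this stands, and it rules out any suggestion that the study should not be run or needs a second arm. It does not rescue the N-of-1 label, the control-group sentence or the claim to hold other effects constant, which are misstatements in the current text. A statistical analysis plan could not supply a comparator that the design lacks.

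It is also fair that women may complete the survey themselves with guidance, and may ask for a different worker (section 7.1). This softens the interviewer problem but does not remove it.

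A reader might infer more than the documents support:

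- *Regression to the mean as a further bias.* Section 5.2 sets no score threshold for entry, so there is no selection on extreme baseline values to produce it.
- *Drop-out as a source of change.* Where the same women are compared before and after, loss mainly limits whom the result represents.
- *Any shift, from any source, will be announced as an effect.* That is a prediction. The protocol does not say how change will be attributed at the forum, and only a large enough shift would be significant.
- *The percentages above as error rates of the planned analysis.* They are ordinary power for one paired outcome at an assumed alpha. The plan is a MANOVA on several outcomes, and women are grouped by health worker.

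**Conclusion.** The point holds as one of labelling and inference. The study is a single-group pre-test/post-test study. It is not an N-of-1 trial, it has no control group, and adjusting for attendance does not hold other effects constant. Retest familiarity, the interviewer and calendar change cannot be separated from an intervention effect, so attributing a difference to the intervention goes beyond what the design can show.

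This conclusion rests on the protocol's description alone and needs no numerical assumption. The figure of about 80% at a drift of 0.22 SD is illustrative and rests on the assumptions listed with it. With no SD given, it cannot be turned into questionnaire items without a further assumption. The text should be corrected because it claims a design property the study lacks, and because the correction changes what the study may conclude.

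**What to change.** Reword four sections:

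- **Section 5.1.** Replace the design sentence with: *A single-group pre-test/post-test design without a concurrent control group will be used.* Delete the control-group sentence.
- **Research Question 2.** Remove the opening clause about other effects and ask: *Do mean outcome scores change from before to after the intervention?*
- **Objective 2.** Write: *Assess change in the following outcomes from before to after the individual and group educational sessions*, then keep the list of outcomes.
- **Section 5.8.2.** State the purpose as: *to assess whether primary or secondary outcomes changed from pre-test to post-test.* Add that conclusions, including those shared at the community forum, concern change over time and not effects attributable to the programme.

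The cost is a more modest claim. Sample, data collection, schedule and analysis stay as they are.
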